## Methods

### Trial Design

The study is a 2-year nonrandomized controlled trial using a 2-arm parallel group design conducted in the community. For the intervention group, we will combine the standard palliative care treatment with a community promoter’s intervention; the control group will benefit from standard palliative care.

Intervention and control group participants will be patients under the community palliative care team’s supervision living in 2 areas with and without community promoter intervention.

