### Setting

The study will be developed in the community, in 2 different geographic areas in Seville, Spain. The main difference between them will be the presence of a community promoter as a part of a new city program called All with You [19].

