### Recruitment Procedure

Potential participants will receive information from palliative care team members. Reasons for declining to participate will be recorded as not interested, too busy, don’t believe in it, and other.

Palliative care teams will arrange an appointment with the patient for the baseline assessment. This first appointment will take place in the patient’s home. At this appointment, written informed consent for participation in the study will be obtained from participants.

Patients assigned to the intervention group will be those living in the San Pablo-Santa Justa area, Seville (60,000 inhabitants), who accepted the community promoter intervention. Patients assigned to the control group will be those living in an area with no community promoter available.

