### Statistical Methods

We will carry out an initial descriptive analysis of variables related to patients’ needs and the profiles of people involved in the social network by degree of kinship.

We will analyze pre- and postintervention data for each group. These will include measures of central tendency (mean), confidence intervals for the 95% average, contingency tables (frequencies), and a linear regression.

To compare the groups, we will compare means. For continuous variables, we will use Student *t* test to compare independent samples with normal distribution and Mann-Whitney *U* test for nonnormal distributions. For discrete variables, we will use Mann-Whitney *U* test. For dichotomous variables (comparison of proportions), we will use Pearson chi-square test. All tests will be carried out with a significance level alpha=.05.

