### Possible Limitations of the Study

As it is not a randomized clinical trial, some selection bias could be considered. If the protocol offers positive results, further randomized investigations will be warranted.

It could be difficult to achieve a clear conclusion if the intervention and control group results are very different, although our results from the descriptive analysis of the intervention group will provide relevant information.

We acknowledge that other clinical or psychosocial variables not included in this protocol can influence patients’ needs and satisfaction. We have chosen basic variables that are recorded in the patient’s medical history and are part of the palliative care approach. Depending on the results, we will consider modifying them for future studies in this line of research.

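### Arms are formed by area of residence and acceptance of the promoter, yet the groups are compared with unadjusted tests, so measured case-mix differences would be read as intervention effect

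*Protocol article*

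**What the plan says.** Trial Design: "The study is a 2-year nonrandomized controlled trial using a 2-arm parallel group design conducted in the community". Setting places the work "in 2 different geographic areas in Seville, Spain" and gives the promoter's presence as the main difference between them. Under Recruitment Procedure, the intervention arm consists of residents of one named area of 60,000 inhabitants "who accepted the community promoter intervention". For the other arm: "Patients assigned to the control group will be those living in an area with no community promoter available". No parallel acceptance step is described for controls.

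Statistical Methods fixes the between-group analysis: "To compare the groups, we will compare means". Continuous variables get Student t or Mann-Whitney according to normality. The next rule begins "For discrete variables, we will use Mann-Whitney", and dichotomous variables get Pearson chi-square, all at alpha .05. The Abstract repeats this. No covariate, matching, weighting or stratification is named. A linear regression appears one paragraph earlier, among the pre- and postintervention analyses for each group, with no outcome, group term or covariates.

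Possible Limitations of the Study grants that "some selection bias could be considered" and that variables outside the protocol may influence needs and satisfaction. It offers no analytic response.

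**The concern.** Unadjusted two-sample tests answer the treatment question only if the groups would have had similar outcomes without the intervention. Allocation by neighbourhood does not secure that, and taking only those willing to accept a promoter in one arm adds a second source of difference. If the two areas differ in age, diagnosis, dependency, loneliness, caregiver burden or prior service use, the difference passes straight into the comparison and is reported as effect.

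This touches every between-group conclusion, including use of health system resources, which the Abstract calls the primary end point. It is also avoidable in part, because the protocol plans to record most of the variables needed to reduce it. The protocol has chosen the tests itself, so this is a stated choice and not a detail left for an analysis plan.

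**Working it through.** **Inputs from the protocol.** 320 per group (Sample Size Calculation); alpha .05 (Statistical Methods), taken as two-sided because sidedness is not stated; one area per arm (Setting, Recruitment Procedure).

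**Inputs assumed, because the protocol gives none.** The size of the pre-existing difference, the correlation of a baseline covariate with outcome, and the intracluster correlation (ICC). Each is shown as a range.

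**1. The plan's own figure.** 700 × 0.65 × (1 − 0.30) = 318.5, close to 320. The number reproduces as a count of available patients, and it is used below as the group size.

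**2. An outcome difference carried over in full, no intervention effect.** In SD units the standard error of the difference in means is √(2/320) = 0.079. For a shift d, the two-sided test rejects with probability 1 − Φ(1.96 − d/0.079) + Φ(−1.96 − d/0.079).

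| Outcome shift d | d/SE | P(p<.05) |
|---|---|---|
| 0.1 SD | 1.26 | 24% |
| 0.2 SD | 2.53 | 72% |
| 0.3 SD | 3.79 | 97% |

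The smallest effect detectable with 80% power is (1.96 + 0.84) × 0.079 = 0.22 SD. An area difference of about that size is as visible to the test as an effect of that size.

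The named intervention area has 60,000 inhabitants, not 100,000. Scaled, the accrual route gives 0.6 × 318.5 = 191 per year, or 382 over two years. At d = 0.2 SD the rejection probability is then 50% or 79%, so the conclusion does not hinge on 320.

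**3. A baseline covariate shifted between areas, no intervention effect.** Only the part correlated with outcome carries over: an outcome shift of r × d. With r = 0.5, a covariate shift of 0.2 SD becomes 0.1 SD in outcome, which is why these figures are lower. Simulation used 2000 runs and 320 per group, with outcome equal to r times the covariate plus noise.

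| Covariate shift | t test, r = 0.5 | t test, r = 0.7 |
|---|---|---|
| 0.1 SD | 10% | 15% |
| 0.2 SD | 23% | 42% |
| 0.3 SD | 48% | 76% |

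Mann-Whitney was within about 2 points of the t test. Regression adjusted for that covariate rejected 4% to 6% of the time throughout. The simulation standard error at 5% is √(0.05 × 0.95/2000) = 0.5 points, so this is the nominal level.

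**4. Between-area variation.** If area is treated as random, the design effect is 1 + 319 × ICC, and the true type I error of the naive test is 2(1 − Φ(1.96/√DE)).

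| Assumed ICC | Design effect | Type I error |
|---|---|---|
| 0.001 | 1.319 | 9% |
| 0.01 | 4.19 | 34% |
| 0.05 | 16.95 | 63% |

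This component remains after covariate adjustment, because with one area per arm the area and the intervention coincide.

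**5. Which outcomes have a baseline value.** Table 1 schedules networks of care, Barthel and Lawton from V0 to V6, and loneliness and Zarit at V0 and V6. Resource use is sought before and at the end of care (Sources of Information and Data Collection). EQ-5D-3L is scheduled only at V6 and satisfaction only at V7, and place of death has no baseline by nature.

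**The case against.** The best defence is that the linear regression may be where adjustment was meant to happen, and that model terms commonly belong in an analysis plan not shown here. The first part does not fit the text: the regression sits with the within-group analyses, before the sentence that opens the group comparison. On the second, the exact covariate list is indeed a matter of judgement, but the protocol does not leave the comparison open. It names the tests. It is silent on whether they apply to final values or to changes.

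Four stronger readings are tempting and are not supported.

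- *Adjustment would isolate the effect of REDCUIDA.* It would not. It deals with measured case mix only. Area, and willingness to accept the promoter, stay confounded with the intervention.
- *Effectiveness will be concluded from the uncontrolled intervention-group series.* The limitations section says only that "our results from the descriptive analysis of the intervention group will provide relevant information". It also calls for later randomized work if results are positive.
- *All patients enter on extreme scores, so regression to the mean is built in on every scale.* Eligibility asks for any of the listed conditions, some of which are not scores.
- *Every covariate is already in hand, so only wording changes.* Three outcomes have no baseline. The V0 referral and requirements sheets are completed by the promoter, whom the control area lacks. Recruitment Procedure describes a baseline visit arranged by the palliative care teams but does not say which scales it records.

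It also stands that the larger percentages need a difference that carries over in full. A covariate shift of the same nominal size does less damage.

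**Conclusion.** The point holds for measured case mix. As written, the between-group comparison takes no account of baseline differences in a design that invites them. Depending on whether the assumed 0.1 to 0.3 SD is an outcome difference or a covariate shift with correlation 0.5, the chance of a spurious significant result is about 24% to 97% or about 10% to 48%, against a nominal 5%. Adjustment restores roughly 5% for the covariates it includes. These sizes rest on assumed imbalances and correlations; the protocol supplies neither, so they show sensitivity and do not predict what will happen.

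A reader might infer that the plan's true type I error is 34%. That figure needs an ICC of exactly 0.01, and it describes a limit of having one area per arm that no analysis of these data can remove. It belongs in the interpretation and is no argument for adjustment.

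**What to change.** - Make the main between-group comparison a regression of the follow-up value on group, with the model chosen by outcome type. Adjust for age, sex, diagnosis, baseline Barthel and Lawton, and the baseline value of the same outcome where one is collected (needs and network measures, ESTE II, Zarit, resource use).
- For EQ-5D-3L, satisfaction and place of death, adjust for the other baseline covariates only.
- Confirm that the palliative care teams' baseline visit records the same scales in controls.
- Do not require Zarit in every model, so that patients without a main caregiver are kept.
- Base the effectiveness conclusion on the adjusted difference. State that with one area per arm it cannot separate area, or acceptance of the promoter, from the intervention, and that intervals are conditional on these two areas.
- If between-area variation is quantified, give a range of ICCs and say that adjustment does not remove it.

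The cost is a little more analysis work, a check on what controls have recorded at baseline (and added collection there if the scales are missing), and a more cautious conclusion. Fixing the covariates before outcomes are seen matters, since a list chosen afterwards would carry little weight.

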**Conclusions:**

The results of this study will provide evidence of the benefit of the REDCUIDA protocol on the development and assessment of networks of compassionate communities at the end of life. It will provide information about clinical and emotional improvements, satisfaction, proxy burden, and health care resource consumption regarding patients in palliative care.

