## Results

This is a 2-year nonrandomized trial. The protocol has been approved by the Clinical Research Committee of Andalusian Health Service. The community promoter has been identified and has received an expert community-based palliative care course (550 hours). The community promoter will start making contacts in the community and the palliative care teams involved in the research project.

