## Discussion

### Beneficiary Population

Results from this study would be applicable among a vast population, including palliative care patients in developing countries. It is known that 7000 people per million population globally die each year, 2500 per million die of cancer, and approximately 4500 per million die in the final stage of any nononcologic illnesses [41]. It is estimated that 65% of this population will need specialized palliative care.

If our results confirm that community social networks improve patients’ and families’ satisfaction at the end of life and correlates with the best use of health system resources, new palliative care systems may be developed.

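### One area and one promoter per arm: the between-group tests at alpha=.05 and the stated 80% power hold only for these two areas and this promoter

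*Protocol article*

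**What the plan says.** **Areas and arms.** The Setting section places the study "in 2 different geographic areas in Seville, Spain". Trial Design describes patients "living in 2 areas with and without community promoter intervention". Recruitment Procedure fixes the arm by residence. The intervention group are "those living in the San Pablo-Santa Justa area, Seville (60,000 inhabitants), who accepted the community promoter intervention", and for the other arm: "Patients assigned to the control group will be those living in an area with no community promoter available". Read together, this is one area per arm.

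**Promoter.** The Results section refers to one person: "The community promoter has been identified and has received an expert community-based palliative care course". The Abstract has this promoter deliver the seven sessions.

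**Tests.** Statistical Methods compares the groups with Student's t test, the Mann-Whitney U test or Pearson's chi-square test, each with the patient as the unit, and closes with "All tests will be carried out with a significance level alpha=.05". The Abstract gives 80% power with 320 patients per group.

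**Conclusions announced.** The Abstract's Conclusions state: "The results of this study will provide evidence of the benefit of the REDCUIDA protocol". Beneficiary Population in the Discussion goes further: "Results from this study would be applicable among a vast population, including palliative care patients in developing countries".

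**Limitations.** Possible Limitations of the Study names selection bias and unmeasured clinical or psychosocial variables. It mentions neither the single area per arm nor the single promoter.

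**The concern.** Patients in one area share local resources and palliative care provision and, in the intervention arm, the same promoter. Several outcomes, such as palliative team visits and telephone calls, depend directly on local provision. A patient-level two-sample test counts only the variation between patients. Whatever separates these two areas, or this promoter from another, goes into the group difference and is left out of its standard error.

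This matters because the announced conclusion is about the REDCUIDA protocol in general. A significant group difference could come from an ordinary difference between two districts, or from one person's skill, at well above the nominal 5% rate.

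**Working it through.** **Inputs.** From the protocol: 2 areas, so 1 per arm (Setting, Trial Design, Recruitment Procedure); 1 promoter (Results); n = 320 per arm (Sample Size Calculation); alpha = .05 (Statistical Methods), taken as two-sided because sidedness is not stated; 80% power (Abstract). Assumed: ICC values of 0.001, 0.005, 0.01 and 0.05, because the documents give none.

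**The plan's own figure.** The 320 reproduces as a head count of available patients: 700 x 0.65 = 455, and 455 x (1 - 0.30) = 318.5, or about 320. No standard deviation, baseline rate, design effect or ICC enters. The 80% power is therefore not derived in that section.

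**Degrees of freedom.** Between-area degrees of freedom are 2 areas - 2 arms = 0. The linear regression listed in Statistical Methods cannot help, because an area term is identical to the treatment term.

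**Variance of the group difference.** With one area of n patients per arm and total variance sd²:

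Var(difference) = (2 sd²/n) x DE, where DE = 1 + (n - 1) x ICC = 1 + 319 x ICC.

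The patient-level test in effect takes DE = 1. Then:

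- true type I error of the nominal 5% test = 2 x [1 - Phi(1.96/sqrt(DE))];
- power at a true 5% level, for an effect with 80% power under independence = Phi(2.80/sqrt(DE) - 1.96), where 2.80 = 1.96 + 0.84, treating the ICC as known;
- effective n per arm = 320/DE.

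| Assumed ICC | DE | SE multiplier sqrt(DE) | True type I error | Effective n per arm | 80% becomes |
|---|---|---|---|---|---|
| 0 | 1 | 1 | 5.0% | 320 | 80% |
| 0.001 | 1.319 | 1.15 | 8.8% | 243 | 68% |
| 0.005 | 2.595 | 1.61 | 22.4% | 123 | 41% |
| 0.01 | 4.19 | 2.05 | 33.8% | 76 | 28% |
| 0.05 | 16.95 | 4.12 | 63.4% | 19 | 10% |

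A simulation of the t test (20,000 runs) gave type I error of 5.0% at ICC 0, 34.1% at 0.01 and 63.8% at 0.05, in agreement with the formula.

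**More patients do not help.** As n grows, Var(difference) tends to 2 x ICC x sd², not to zero. At ICC 0.01 the standard error cannot fall below sqrt(0.02) = 0.14 sd. The patient-level standard error at n = 320 is sqrt(2/320) = 0.079 sd.

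**The case against.** **These are two named areas, not a sample of areas.** If inference is meant only for these two areas, a difference between them is a fixed quantity. It biases the comparison but does not make the patient-level standard error wrong. This stands. A reader might infer that the standard error and p value are wrong on any reading; the documents do not support that. The standard error falls short only when the conclusion reaches beyond these areas and this promoter, which is where the Abstract's Conclusions and Beneficiary Population take it.

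**Non-randomised bias is already acknowledged.** In part. The limitations section mentions selection bias and unmeasured variables and calls for randomised work if results are positive, and the Discussion's closing conclusions are more cautious than the Abstract's. Neither names the single area per arm or the single promoter, and adjusting for patients' baseline values would not supply the missing between-area variation.

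**The ICC is invented.** The size of the inflation does rest on an assumed range, and the mildest value shown gives only about 9%. The zero degrees of freedom and the inseparability of protocol, promoter and area need no ICC.

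**The sentence on alpha covers every test.** Within-group pre/post analyses are not area-against-area contrasts, so this point does not touch them.

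**The 80% is itself unsupported.** Correct. A reader might take 41% or 28% as this trial's real power. That cannot be said, because 320 is a head count and the 80% has no stated basis. The last column shows what happens to any comparison that has 80% power under independence.

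**Conclusion.** The point holds for the between-group comparison. As written, alpha=.05 and 80% power are stated without condition, for a design with one area per arm and one promoter. For a conclusion about the REDCUIDA protocol in general, the 5% level is correct only if variation between areas and promoters is exactly zero. Under assumed ICCs of 0.001 to 0.05 with 320 patients per area, the true two-sided type I error runs from about 9% to about 63%. The trial's own data cannot narrow that range, and neither can more patients in the same two areas. The figures rest on the assumed ICCs, equal arms of 320 and a two-sided test. The fault does not invalidate the study as an evaluation in these two areas, but it should be fixed because it limits what the study may conclude.

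**What to change.** 1. **Abstract (Methods) and Statistical Methods:** state that between-group p values, confidence intervals, alpha and power are conditional on these two areas and this promoter, and exclude variation between areas.
2. **Statistical Methods:** for between-group differences in means and proportions, add a sensitivity confidence interval with the standard error multiplied by sqrt(1 + (n - 1) x ICC), where n is the number analysed per area. Fix the ICC range in advance, include 0.001 to 0.05, and label it as assumed. If the arms differ in size, inflate each arm's variance by its own factor. The multiplier does not carry over directly to the Mann-Whitney test, so confine it to means and proportions.
3. **Possible Limitations of the Study:** add the single area per arm and the single promoter.
4. **Abstract (Conclusions) and Beneficiary Population:** limit the conclusion to this promoter in this area, and remove the statement on applicability to developing countries.

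The cost is a few sentences and one table, with no more patients; the stated precision and scope become less favourable. Adding further control areas is not part of the required change. It would let between-area variation be estimated among controls, but it is not clearly cheap and would still leave the protocol inseparable from one promoter.

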### Ethical Considerations

Ethical approval for this study was given by the Clinical Research Committee of Andalusian Health Service, Spain (CI 1020-N-17), in June 2018. The study uses informed consent sheets approved by the Clinical Research Committee of Andalusian Health Service, Spain. The right to guarantee data protection will be fulfilled.

## Results

This is a 2-year nonrandomized trial. The protocol has been approved by the Clinical Research Committee of Andalusian Health Service. The community promoter has been identified and has received an expert community-based palliative care course (550 hours). The community promoter will start making contacts in the community and the palliative care teams involved in the research project.

## Discussion

### Beneficiary Population

Results from this study would be applicable among a vast population, including palliative care patients in developing countries. It is known that 7000 people per million population globally die each year, 2500 per million die of cancer, and approximately 4500 per million die in the final stage of any nononcologic illnesses [41]. It is estimated that 65% of this population will need specialized palliative care.

If our results confirm that community social networks improve patients’ and families’ satisfaction at the end of life and correlates with the best use of health system resources, new palliative care systems may be developed.

